## Methods/Design

### Design

This study will be a multicentre prospective randomised clinical trial. Eligible patients will be randomised for either ultrasound-guided surgery (USS) or palpation-guided surgery (PGS).

### Subjects and patient selection

One hundred and twenty patients will be recruited over a period of six months at a university medical center and several medium to large hospitals in the Netherlands. All women aged 25-75 yrs who are diagnosed with palpable early-stage (T1-2N0-1) invasive breast cancer in the trial centres will be invited to participate in this study. Breast cancer will be diagnosed with physical examination, mammography (2R) and US, and occasionally MRI of the breast and axilla. The diagnosis of invasive (ductal or lobular) breast cancer will be established with image-guided core needle biopsy or cytological puncture. All patients will be discussed in a multidisciplinary team, and suitable for BCT according to national guidelines. Participants will not have a history of prior mammary surgery of the affected breast, radiation therapy or neo-adjuvant therapy. Participants will have ASA Classification I-III and will be well-informed having signed an informed consent form.

Full ethical approval is obtained for this study from the Investigational Review Board of the VU University Medical Centre, including the Medical Ethical Review Board.

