**Methods/design:**

In this prospective multicentre randomised controlled clinical trial, 120 women who have been diagnosed with palpable early-stage (T1-2N0-1) primary invasive breast cancer and deemed suitable for breast-conserving surgery will be randomised between ultrasound-guided surgery and palpation-guided surgery. With this sample size, an expected 20% reduction of resected breast tissue and an 18% difference in tumour-free margins can be detected with a power of 80%. Secondary endpoints include cosmetic outcomes and quality of life. The rationale, study design and planned analyses are described.

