## Background

Breast cancer is the most common cancer among women in the western world. It affects women of all ages and the lifetime risk of developing invasive breast cancer is 12-13%. The 5-year disease-free survival rate for node-negative breast cancer, however, is excellent (98%). Breast cancer surgery has changed dramatically over the past few decades. Breast-conserving therapy (BCT) was introduced in the 1970s and refers to the surgical removal of the breast tumour in all cases followed by radiotherapy to eradicate residual tumour cells. The introduction of the sentinel node procedure for nodal staging has avoided the morbidity of axillary lymph node dissection in the majority of patients. Several trials demonstrated comparable results with regard to disease-free and overall survival between mastectomy and BCT combined with radiotherapy, and the latter has become the standard of care for early-stage breast cancer. According to national guidelines, 75% of breast cancer patients are suitable for BCT. The main advantage of BCT over mastectomy is preservation of the breast with improved cosmetic outcomes [1-5].

Breast cancer and its treatment have many adverse side-effects, which may be both physical and psychological. Psychological distress is common in the breast cancer population and affects approximately 30% of patients. Fear of disease recurrence, concerns about future health and interruption of life plans often lead to anxiety and depression.

The cosmetic result is also a major determinant of psychological distress. Cosmetic outcome of the breast has a large impact on body image, and studies have shown that women with poor cosmetic outcomes as determined by pronounced breast asymmetry and skin alterations are impaired in their self-esteem, feelings of sexuality and quality of life. Furthermore, these women are more likely to feel stigmatised and have more symptoms of depression. Focusing on the best achievable cosmetic result will lead to a decrease in psychological distress [6-9].

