#### Cosmetic Analysis

During the follow-up visits three and six months after surgery, the cosmetic outcome will be evaluated. Standard 4-point view digital photographs, including the suprasternal notch, will be taken. These photographs will be scored by a panel consisting of six persons (including both professionals and non-professionals). The items scored will be the overall result, the appearance of the surgical scar, breast size, breast shape, nipple position and the shape of areola. The treated breast will be compared to the untreated breast, using the 4-point Lickert scale. Objective cosmetic analysis will be performed with the Breast Retraction Assessment (BRA) or comparable objective software. BRA values are calculated using measurements from the frontal view photographs and quantity the amount of retraction of the treated breast compared to the healthy contralateral breast by measuring nipple displacement. A large BRA value corresponds to increased asymmetry between the breasts and to poor cosmetic results (Figure 7). Subsequently, the patients' opinions concerning cosmetic outcome will be assessed using patient self-evaluation. Long-term follow-up (3 yrs) will probably be studied in a future research project.

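### The panel and BRA cosmetic scores need an untreated contralateral breast, which eligibility does not secure and no pre-operative photograph replaces

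*Protocol article*

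**What the plan says.** Under Subjects and patient selection, the protocol article opens entry broadly: "All women aged 25-75 yrs who are diagnosed with palpable early-stage (T1-2N0-1) invasive breast cancer in the trial centres will be invited". It then narrows it: "Participants will not have a history of prior mammary surgery of the affected breast, radiation therapy or neo-adjuvant therapy". The laterality is attached to prior surgery. The radiotherapy and neo-adjuvant clauses name no side. No requirement for unilateral disease appears.

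Under Cosmetic Analysis, the panel rule is: "The treated breast will be compared to the untreated breast, using the 4-point Lickert scale". BRA is described as quantifying "the amount of retraction of the treated breast compared to the healthy contralateral breast by measuring nipple displacement". A third measure has no stated contralateral reference: "the patients' opinions concerning cosmetic outcome will be assessed using patient self-evaluation". On timing: "During the follow-up visits three and six months after surgery, the cosmetic outcome will be evaluated". Table 1 and the Timeline section agree with this: cosmetic measurements and photographs appear only at three and six months, whereas the quality-of-life questionnaire is also completed before surgery.

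The abstract sets the status of these outcomes: "Secondary endpoints include cosmetic outcomes and quality of life".

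**The concern.** Two stated provisions do not fit together. The scoring section presupposes a healthy, untreated contralateral breast, and the eligibility section does not secure one. No rule says how to score a woman who lacks it.

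The effect on the score depends on the woman. An altered contralateral breast makes BRA record asymmetry that the study operation did not cause. Surgery on both breasts can hide asymmetry that it did cause. After contralateral mastectomy, BRA cannot be calculated at all.

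The Discussion and Conclusion section proposes combining the panel evaluation and BRA into one overall cosmetic score. Both components lean on the same reference, so neither can stand in for the other when that reference is missing.

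The lack of a pre-operative photograph reaches further. Even in a woman whose other breast is untouched, asymmetry present before surgery enters the three- and six-month scores and cannot be removed.

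**Working it through.** **Who can be enrolled without the reference**

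- Synchronous bilateral cancer: not excluded, because unilateral disease is not required.
- Earlier contralateral reduction, implant, benign excision or mastectomy without radiotherapy: not excluded, because the surgical clause covers only the affected side.
- Earlier contralateral breast-conserving therapy: arguably already excluded. The Background says that this therapy "refers to the surgical removal of the breast tumour in all cases followed by radiotherapy to eradicate residual tumour cells", and the radiotherapy exclusion names no side.

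**Which measures depend on the other breast**

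- BRA: yes, by definition.
- Panel items: yes, by the stated comparison, although the scar item has no natural counterpart on an unoperated breast.
- Patient self-evaluation and the personalised interview: no contralateral reference is stated.
- Resected volume and margin status: no.

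**The plan's own figure**

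The target of 120 is not in dispute here; it supplies the 60 per arm used below. It follows from margin involvement of 22.5% versus 5% (Sample size calculation), with two-sided 5% significance assumed, 80% power and no continuity correction. The mean proportion is 0.1375.

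n = [1.96·√(2·0.1375·0.8625) + 0.8416·√(0.225·0.775 + 0.05·0.95)]² / 0.175²
= (0.9546 + 0.3964)² / 0.030625 = 59.6, hence 60 per arm.

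The article gives no power statement for the cosmetic endpoint.

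**If scores are lost**

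Let f be the share of women without a valid reference. The documents give no value, so f is an assumption. With n = 60(1 − f) per arm and a continuous score in SD units:

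- detectable difference at 80% power = (1.96 + 0.8416)·√(2/n)
- power at the difference detectable with 60 per arm (0.511 SD; 0.5115 unrounded) = Φ(0.5115/√(2/n) − 1.96)

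| f | Women lost of 120 | n per arm | Detectable difference (SD) | Power at 0.511 SD |
|---|---|---|---|---|
| 0 | 0 | 60 | 0.511 | 80.0% |
| 2% | about 2 | 58.8 | 0.517 | 79.2% |
| 5% | 6 | 57 | 0.525 | 78.0% |
| 10% | 12 | 54 | 0.539 | 75.7% |

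**If distorted scores are kept**

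Suppose BRA in the affected women carries extra variation of k SD, again an assumption. Total variance becomes 1 + f·k², and power is Φ(2.8016/√(1 + f·k²) − 1.96).

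- k = 1: variance 1.05 (f = 5%) or 1.10 (f = 10%); power about 78% or 76%.
- k = 2: variance 1.20 or 1.40; power about 72% or 66%.

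Under these assumptions, keeping distorted scores costs about as much as losing them when k = 1, and more when k = 2.

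**Baseline asymmetry**

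Its cost cannot be computed from the documents. It depends on the correlation between pre-operative and follow-up BRA, which is not given.

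**The case against.** The strongest reply has four parts.

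1. **The criterion is not blind to the other side.** A reader might infer that eligibility screens only the affected breast. The text does not support that: the radiotherapy exclusion names no side, and on its natural reading it removes earlier contralateral breast-conserving therapy. This stands, and it narrows the affected group to bilateral disease and non-irradiated contralateral surgery.

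2. **Randomisation protects the comparison.** A reader might infer bias between the arms. Contralateral history precedes randomisation, which is stratified by institute, so these women are expected equally in both arms. Pre-existing asymmetry is balanced in expectation too. A baseline photograph therefore buys precision and interpretability; it is not a condition for a valid comparison. This also stands.

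3. **Not all cosmetic data are affected.** Self-evaluation and the interview remain usable, and cosmesis is a secondary endpoint on which the sample size does not rest. This stands.

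4. **The article is a condensation.** A longer eligibility list, or a scoring rule for such women, may sit in the full protocol or analysis plan. This stands only in part. The article does not merely omit a detail: it states a one-sided surgical exclusion and a scoring reference that this exclusion does not guarantee.

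**Conclusion.** The mismatch is real but limited. The article as written admits some women for whom the panel comparison and BRA have no valid reference, and it describes no pre-operative image that could replace it. The effect is added noise, dilution towards no difference, or a few missing scores in a secondary endpoint.

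If 2-10% of the 120 women lost their scores, power on a continuous cosmetic score would drop from 80% to about 79-76%. If distorted scores were kept, with extra variation of 2 SD in 5-10% of women, it would drop to about 72-66%. Both ranges rest on assumed shares, and the second also on an assumed spread; nothing in the documents fixes either.

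It would go too far to conclude that the trial's cosmetic results as a whole are invalid, that the arms are unfairly compared, or that the primary volume endpoint or the margin result is touched.

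**What to change.** 1. Keep these women in the trial for volume and margins, where they are fully informative. Excluding them at entry would give up primary-endpoint data to tidy a secondary endpoint.
2. Pre-specify that BRA and the contralateral-referenced panel items are analysed only in women with an untreated contralateral breast, identified from the baseline medical history that Table 1 already lists. Because the set is defined by a pre-randomisation characteristic, the randomised comparison within it is preserved. Self-evaluation and the interview stay in all women.
3. State explicitly whether the radiotherapy exclusion applies to either breast.
4. Take the same four-view photographs before surgery, when patients already complete the questionnaire, and adjust BRA for baseline asymmetry. This image cannot be recovered after the operation.

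The cost is slightly fewer women in the cosmetic analysis, a sentence or two of text and one extra photograph set at an existing visit.

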### Study procedures

#### Pre-operative

Prior to surgery, patients will be informed about this trial by both written and oral explanations. Informed consent will be obtained. Subsequently, the patients will complete the quality of life questionnaire, EORTC QLQ-C30/-BR23. The principal investigator will randomly assign the participants to either of the two treatment modalities by using a digital randomisation program. Group I will undergo PGS and group II USS. Stratification by institute will be performed to ensure balanced allocation between the two treatment modalities in each institution.

#### Surgery

Surgery will be performed under general anaesthesia by dedicated oncological breast surgeons or by surgical residents under their close supervision. The surgery will start with the axillary procedure. In clinically node-negative patients surgery of the axilla consists of a single sentinel node procedure. For the sentinel node procedure, a triple method will be used, consisting of combined lymphoscintigraphy (Tc99m colloidal albumin [Nanocoll^®^]), Patent Blue V^® ^(Guerbet, Aulnay-Sous Bois, France) dye injection, and gamma probe detection[2]. In some institutions, the sentinel node is sent for frozen section study, and if metastases are diagnosed, axillary lymph node dissection is performed during the same procedure. Node-positive patients who are pre-operatively confirmed by US-guided cytological puncture will undergo an axillary lymph node dissection. Axillary lymph node dissection is a routine procedure, consisting of a classic level I and II dissection. After the axillary procedure, surgery of the breast is performed. The aim in both the USS-group and the PGS-group will be to obtain a rim of 1 cm of healthy adjacent breast tissue around the malignant breast lesion.

#### Palpation-guided surgery

In the PGS group, tumour excision will be guided by the palpation of the surgeon in the standard manner. The index finger will be used to palpate the mass, retract it and guide the dissection. In this procedure, the adequacy of the resection is based on the experience of the surgeon without objective imaging during surgery.

#### Ultrasound-guided surgery

In the USS group, tumour excision will be performed by the surgeon with US guidance in collaboration with an experienced radiologist. Prior to surgery, the surgeon will carry out an US of the lesion under direct supervision of the radiologist. During the surgery, the radiologist will be present either in the operating theatre or in the radiology department. The surgical procedure will start with the standard sentinel node procedure, after which the US-guided lumpectomy will be performed. USS will be performed using a THI 14-MHz US probe (Toshiba Viamo portable ultrasound system, Japan). The probe is coupled to a mobile US unit and covered with a sterile sheath that enables it to be used in the surgical wound. The lesion will be carefully localised in the breast by palpation and US imaging (Figure 2). The localisation of the lesion will be compared to the pre-operative images. The breast tissue will be positioned in such a way that the lesion is located as close to the skin surface as possible, and the breast will be fixed in that position throughout the procedure by hand or using tape. The tumour size, lesion-to-skin distance and lesion-to-fascia distance will be measured in millimetres by US. The localisation of the tumour will be precisely marked on the skin, and the incision will be made. After the incision, the skin over the lesion will be dissected from the subcutaneous tissue, and the US probe will be positioned in the wound to reassess the position of the lesion. Also, the index finger will be used to palpate the mass, retract it and guide the dissection. Dissection is continued posteriorly in the plane between the breast and the pectoral fascia. To achieve adequate margins, US will be applied repeatedly in the wound from different angles while continuously monitoring the location and depth of the tumour (Figure 3, 4). Subsequently, a spherical lump of breast tissue will be excised. It is recommended to place a "pool suture" around the tumour under US guidance to facilitate the excision. After completion of the excision, the specimen will be scanned ex vivo by US to assess the completeness of the excision (Figure 4, 5).

**Figure 2 F2:**
[figure not shown]
**Tumour localising by ultrasound imaging**.

**Figure 3 F3:**
[figure not shown]
**Ultrasound image on screen**.

**Figure 4 F4:**
[figure not shown]
**The ultrasound is applied repeatedly in the wound**.

**Figure 5 F5:**
[figure not shown]
**After excision, completeness of the specimen is checked by ultrasonography**.

The orientation of the specimen will be preserved with marking sutures such that positive resection margins can be identified and re-excised if necessary. Haemostasis will be obtained, and drains will not be used. If requested, titanium clips will be placed in each quadrant to guide radiotherapy. Subcutaneous tissue will be closed with dissolvable stitches, and the skin will be closed with stitches or staples.

### Outcome parameters (Table 1)

**Table 1 T1:** Outcome Parameters

Patient	Age
	Race
	Breast size
	Medical history
**Pre-operative**	Experience of the surgeon
	Complications
	Duration of the procedure
	Cost of the procedure
	Type of surgery in the axilla (SN or ALND)
	Adequate margins based on US ex vivo
	Specimen volume (fluid displacement

**Histological**	Surgical specimen volume
	Tumour volume (diameter) within the specimen
	Margin status
	Shortest distance to the nearest resection margin

**Adjuvant therapy**	Radiotherapy (dose, boost)
	Chemotherapy
	Hormonal therapy

**Two weeks post-operatively**	(Wound) complications

**Three and six months post-operatively**	Cosmetic outcome measurements
	Quality of life (questionnaires)

#### Perioperative parameters

The experience of the surgical residents, complications, the duration of procedure (i.e. time from the incision to wound closure; time needed for the axillary surgery is excluded) and costs of the procedure are registered.

After excision the volume of the specimen will be measured in the operating room by fluid displacement. The specimen will be submerged in an Erlenmeyer flask filled with normal saline at 37^176;^C. The volume of fluid displaced equals the volume of the specimen. If re-excision is performed during the surgery, the volume of the reexcised specimen will be calculated separately and subsequently added to the originally excised specimen.

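### Procedure duration appears to be timed from the breast incision, which leaves out ultrasound work done just before it and tends to favour the ultrasound arm; the start of the clock needs defining

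*Protocol article*

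**What the plan says.** All references are to the protocol article. Table 1 lists "Duration of the procedure" among the outcome parameters, with cost as a separate item. The section Perioperative parameters defines duration as "time from the incision to wound closure; time needed for the axillary surgery is excluded", and adds only that "costs of the procedure are registered". It does not say which incision starts the clock, or how cost is built up.

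The Surgery section has the axilla operated on first in both arms, and then the breast. For the ultrasound arm (USS), the Ultrasound-guided surgery section then describes the equipment ("The probe is coupled to a mobile US unit and covered with a sterile sheath"), localisation ("The lesion will be carefully localised in the breast by palpation and US imaging"), comparison with the pre-operative images, and positioning and fixing of the breast. Next come the measurements ("The tumour size, lesion-to-skin distance and lesion-to-fascia distance will be measured in millimetres by US") and the marking: "The localisation of the tumour will be precisely marked on the skin, and the incision will be made". A separate scan takes place earlier: "Prior to surgery, the surgeon will carry out an US of the lesion under direct supervision of the radiologist".

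For the palpation arm (PGS), the Palpation-guided surgery section describes excision guided by the surgeon's finger. It mentions no imaging, measuring or marking before the incision.

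**The concern.** A duration outcome compares two techniques fairly only if the clock covers the same stages of work in each. Here some of what the technique adds is done in theatre immediately before the breast is opened. If the clock starts at that opening, and axillary time is excluded, this work falls in neither interval. USS would then look quicker relative to PGS than it is.

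Duration is not the primary endpoint (resected volume) and is not among the secondary endpoints named in the abstract. It still bears on adoption. The Discussion cites shorter operating room time as an advantage of ultrasound guidance, there over wire-guided excision of nonpalpable tumours, and it names the arranging of a radiologist's presence in theatre as a possible restriction.

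**Working it through.** The article states no duration, standard deviation or cost rate, so there is no figure to reproduce. The check sets the timing rule against the order of steps.

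**Step 1. Is each step inside the recorded interval?** Reading A starts the clock at the breast incision. Reading B starts it at the axillary incision and subtracts axillary time.

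| Step | Described for | Reading A | Reading B |
|---|---|---|---|
| Supervised scan before surgery | USS | no | no |
| Localisation by ultrasound, comparison with images | USS | no | yes |
| Positioning and fixing the breast | USS | no | yes |
| Three ultrasound measurements | USS | no | yes |
| Skin marking | USS | no | yes |
| Repeated scanning in the wound | USS | yes | yes |
| Ex vivo scan of the specimen | USS | yes, if before closure | yes, if before closure |
| Excision and closure | both | yes | yes |

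The sheathing of the probe is described before localisation, but its moment is not fixed. It could be done during the axillary procedure, so I leave it out of the table.

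**Step 2. Which reading is more natural?** The Ultrasound-guided surgery section uses the same term for the breast incision, made directly after marking. That supports reading A. The duration definition itself does not settle it.

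**Step 3. Direction and size under reading A.** Let T be the time from the end of the axillary procedure to closure, R the recorded time, and u and p the mean uncounted minutes in USS and PGS. Then T = R + u in USS and T = R + p in PGS, so

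recorded difference (USS − PGS) = true difference − (u − p).

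Write m = u − p. The text describes ultrasound work before the incision in USS and none in PGS, so m is expected to be positive. Its value is not given. With an assumed m (illustration only), the true difference is the recorded difference plus m, in minutes:

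| Recorded USS − PGS | m = 2 | m = 5 | m = 10 | m = 15 |
|---|---|---|---|---|
| −5 | −3 | 0 | +5 | +10 |
| 0 | +2 | +5 | +10 | +15 |
| +5 | +7 | +10 | +15 | +20 |

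A recorded 5-minute advantage for USS disappears at m = 5 and reverses above it.

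**Step 4. Mixed readings.** If a fraction f of patients is timed under reading A and the rest under reading B, the understatement is f × m. With f = 0.5 and m = 10 it is 0.5 × 10 = 5 minutes. Stratification by institute balances f between arms but does not remove the understatement.

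**Step 5. Does it reach the saving in the Discussion?** That figure is 5000 × 17.5% = 875 fewer operations, and 875 × € 7 000 = € 6 125 000. No operating time enters it.

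**The case against.** The strongest counter-argument concerns the exclusion clause. Surgery starts with the axilla, so a clock started at the breast incision would have no axillary time to exclude. The clause does real work only under reading B, and under reading B the in-theatre steps are counted. This stands as a genuine ambiguity. It does not rescue the rule, because the clause can equally be a plain clarification and the nearest use of the term points to the breast. A definition that sites can apply in two ways needs repair in any case.

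Three further objections stand in part:

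- Much USS-only work (scanning in the wound, the suture recommended under ultrasound guidance) comes after the incision and is timed. A reader might infer that the rule hides all the time the technique adds; it does not.
- PGS surgeons may palpate and position the breast before cutting, although the short description does not say so. That makes p greater than zero and m smaller, but it supplies no counterpart to ultrasound measurement and marking.
- Incision to closure is an explicit interval, worded the same for both arms. It answers a legitimate question, but not how long the breast procedure takes when one technique adds preparatory steps in theatre.

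A reader might also infer that cost is biased, or that the saving in the Discussion is inflated. Neither is supported. The article states no costing method, and radiologist and equipment costs may be counted separately. The saving rests on avoided re-operations alone.

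**Conclusion.** The point holds in a limited form and is minor. On the natural reading, the definition omits intervention-specific in-theatre work from the duration in the USS arm (60 patients planned) and no described imaging or marking step in the PGS arm, so the comparison tends to favour USS. The direction rests on two assumptions: that the clock starts at the breast incision, and that preparation before the incision takes longer in USS than in PGS. The size cannot be computed from the article; the 2 to 15 minutes above are illustrative. If the clock starts at the axillary incision, the in-theatre steps are counted, and what remains is the risk of inconsistent timing between sites.

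The supervised scan before surgery lies outside operating time on either reading. It is a matter of resource use, not an error in timing the operation. The volume and margin results are untouched.

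**What to change.** Define breast-procedure duration in both arms as running from the end of the axillary procedure, when positioning or localisation of the breast begins, to wound closure. Also record the breast incision, and report breast incision to closure as a second time, so that the usual surgical interval stays available. If procedure cost is calculated from duration, use the longer interval.

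This needs one extra time stamp per operation and one sentence in the protocol. It changes no treatment, eligibility rule or sample size. The price is a duration comparison slightly less favourable to USS.
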